### Oversight and monitoring

#### Composition and responsibilities of the coordinating center and trial steering committee

This trial will be run by dermatologists, dermatological residents, (research) nurses, and PhD students in participating centers. They will be appointed, trained, and overseen by the trial steering committee consisting of the principal investigator, two project leads, a project coordinator, a methodologist, two experts in health technology assessment, a professional representative, a patient representative, and a representative of non-academic hospitals. The trial steering committee regularly meets with executive- and monitoring parties and produces progress reports to the sponsor and funders. The principal investigators, co-investigator, project coordinator, and methodologist conduct data management. All parties involved in the trial, including the participating centers, signed a consortium agreement that simultaneously serves as a clinical trial agreement. This legal document is kept in the trial master file and local investigator site files.

#### Monitoring

Monitoring will be performed in compliance with Good Clinical Practice (GCP), the guideline of the Dutch Federation of University Medical Centers (NFU), and additional regulations, if applicable. The trial sponsor appointed Trialbureau Zorgevaluatie Nederland (www.zorgevaluatienederland.nl/trialbureaus/trialbureau) as the party that will perform monitoring. An independent qualified monitor from this party will have access to the data and source documents of the study and will perform on-site or remote quality checks on the data collection, verification of data, the rights and wellbeing of the patients, and adherence to the study protocol. All sites will be visited by the monitor at least once during the study. Central remote monitoring will occur three months after the first included patient, followed by twice yearly. All monitoring arrangements and other details regarding quality assurance will be bundled in a separate monitoring plan.

#### Adverse event reporting

An adverse event is an undesirable experience occurring to a subject during the study, whether or not considered related to the study activities. As this study’s investigational therapy is already standard clinical practice, we theorize that it can be accurately predicted which adverse events are study related. The known short- and long-term side effects are considered mild. Therefore we consider it safe to not include all adverse events in this study’s dataset. Investigators will instead report the adverse events that are of special interest to this study. A full list can be found in Table 1. All adverse events will be categorized according to MedDRA.

**Table 1 Tab1:** Adverse events of special interest

Adverse events of special interest (AEoSIs)
Sunburn
Photosensitive flare
Polymorfic light eruption
Burning and/or pruritus that requires management
Syncope
Development of skin cancer
Hyperpigmentation
Hypopigmentation
Contact allergy
Development of striae
Development of skin atrophy
Dermatitis perioralis/periorificialis
Folliculitis
Herpes simplex
Tinea incognito
Bacterial infection
Exacerbation of atopic eczema

##### Adverse events of special interest (AEoSI)

An adverse event of special interest is defined as an undesirable experience occurring to a subject during the study, whether or not considered related to the study activities, that is of interest to this study. All AEoSIs reported spontaneously by the subject or observed by the investigator or his staff will be recorded and analyzed (Table 1).

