**Methods:**

A pragmatic, multicenter, PROBE trial will be performed with 1:1 randomization of 316 adult patients with moderate-to-severe AE who have inadequate disease control with topical therapy and who are eligible for optimal topical therapy (OTT) or NB-UVB in combination with OTT as a next step. Participants in the interventional arm will receive a minimum of 3 months of OTT combined with 8 to 16 weeks of NB-UVB. The control group receives 3 months of OTT. Following the interventional phase, follow-up will continue for 9 months. Physician-reported and patient-reported outcomes (according to the Harmonising Outcome Measures for Eczema (HOME) Core Outcome Set) and adverse events are assessed at 4 weeks, 3, 6, 9, and 12 months.

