#### Intervention description

##### NB-UVB

Both outpatient clinic and at-home NB-UVB will be assessed. The ultraviolet emission from phototherapy booths and panels is made possible by UVB lamps. NB‐UVB devices contain fluorescent lamps emitting UVB in the 311 nm to 313 nm range [19].

In the out-patient clinic administration of NB-UVB rays will be executed according to the manufacturer’s instructions by trained nurses. Patients undergoing at-home therapy will receive detailed instructions on the treatment procedure prior to starting NB-UVB. During the course participants will be remotely monitored via the site’s affiliated phototherapy panel supplier, following the local procedure. During administration, all patients will wear protective goggles and cover the genital area to shield the eyes and scrotum/vulva from ultraviolet rays. Administration will occur three times a week.

The patient’s initial dosing and dosage modification during phototherapy will be done according to a standardized study dose regimen (Additional file 2). During NB-UVB treatment, the researcher (or if the researcher is not a physician: the researcher together with a supervising physician) will monitor therapy response and tolerability and determine treatment duration (minimum of 8 weeks, maximum of 16 weeks).

After completing the NB-UVB course and applying 3 months of OTT (as listed below), patients are allowed to take the next step in the AE treatment algorithm if needed, being one of the currently available systemic immunomodulating therapies.

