##### Secondary outcome

Physician-reported clinical signs at 1–3–6–9–12 months:Delta EASIPercentage of patients with EASI50vIGA-AD (range 0–4) [25].Time until a 25% reduction in mean EASI is achievedType, frequency, and quantity of topical therapies usedTime to switch to systemic therapyUse, amount, and duration of rescue medicationPatient-reported symptoms at 1–3–6–9–12 months:PGA (Patient Global Assessment) (range 0–4) [26].POEM (Patient-Oriented Eczema Measure) (range 0–28) [27, 28].NRS-11 (Numeric Rating Scale) for peak itch over the past 24 h (range 0–10) [29].Patient-reported quality of life at 1–3–6–9–12 months:DLQI (Dermatology Life Quality Index) (range 0–30) [30, 31].Patient-reported disease control at 1–3–6–9–12 months:RECAP (recap of atopic eczema) (range 0–28) [32].Patient-reported satisfaction with received treatment:PsoSat (Psoriasis care Satisfaction questionnaire) (range 0–30) [33].Cost-effectiveness at 3 and 12 months:EQ-5D-5L (EuroQol 5D 5L) (range 11,111–55,555) [34].Adapted iMCQ (iMTA Medical Consumption Questionnaire) [35].Adapted iPCQ (iMTA Productivity Cost Questionnaire) [35].Percentage of patients who achieve Treatment Target goals for AE at 3 (EASI50, delta PGA ≥  − 1), 6–9–12 months (EASI ≤ 7.0, PGA ≤ 2) [36].Adverse events of special interest (AEoSIs) and serious adverse events (SAEs) at 1–3–6–9–12 monthsPercentage of therapy failures and dropouts and reasons at 1–3–6–9–12 months, categorized according to Medical Dictionary for Regulatory Activities (MedDRA).

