#### Participant timeline

After screening and informed consent, participants will be randomized in the NB-UVB + OTT or OTT group. Study participation will entail 6 study visits. The baseline visit will take place before therapy starts. The follow-up visits are at 4 weeks, 3, 6, 9, and 12 months. Visits may be rescheduled within 1 month of the initial planning. Extra visit(s) will take place in case of therapy switch or stop. Patients in the NB-UVB + OTT group will undergo phototherapy 3 times a week for a planned period of 12 weeks from baseline, with a possible range of 8 to 16 weeks, depending on therapy response. Therapy duration will be determined in accordance to standard clinical practice. NB-UVB can be applied in the outpatient clinic or at home. Participants in both groups will apply daily OTT for a minimum of 3 months. Patients will be asked to keep all tubes of used OTT (excluding emollients) and bring them to the study visits. During the visits, data about NB-UVB and OTT will be collected. Patients will be asked for possible SAEs and AEoSIs with details such as start and stop date, intensity/severity of adverse events, probability of relation with NB-UVB + OTT or OTT, whether the allocated therapy was interrupted, and co-medications. During all visits, a physical examination by a blinded outcome assessor will take place to assess disease severity. Additionally, a set of questionnaires will be sent to the patient. The questions can be filled out on an electronic device, either at home or during the study visit in the outpatient clinic. At baseline, 3 months, and 12 months, an additional set of questionnaires regarding disease burden on productivity and medical costs will be filled out (Fig. 1). Subjects that have completed trial participation or have discontinued prematurely will be referred back to standard eczema care.

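### AEoSIs noted outside the common visits enter the analysis, and clinic NB-UVB gives more chances to note them, so the comparison of mild shared events is at risk of unequal ascertainment

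*Protocol article*

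**What the plan says.** Two routes of capture are described in the protocol article.

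- **Questioning at visits.** Under Participant timeline, "Patients will be asked for possible SAEs and AEoSIs with details such as start and stop date, intensity/severity of adverse events", together with relation to the allocated therapy. The schedule is common to both arms: "The follow-up visits are at 4 weeks, 3, 6, 9, and 12 months". The abstract agrees ("adverse events are assessed at 4 weeks, 3, 6, 9, and 12 months"), and the Secondary outcome section lists AEoSIs and SAEs at the same times.
- **Open-ended capture.** Under Adverse events of special interest (AEoSI), "All AEoSIs reported spontaneously by the subject or observed by the investigator or his staff will be recorded and analyzed". No time window is set and no distinction is made by where the report came from.

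Contact with staff differs by arm. In the NB-UVB section, "Administration will occur three times a week", for 8 to 16 weeks. Trained nurses run the sessions in the outpatient clinic. For home treatment, "During the course participants will be remotely monitored via the site’s affiliated phototherapy panel supplier, following the local procedure". The same section has the researcher monitor tolerability during NB-UVB. No counterpart is stated for OTT alone.

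**The concern.** Safety of NB-UVB + OTT against OTT is one of the stated objectives. The Adverse event reporting section leaves other non-serious adverse events out of the dataset, so AEoSIs carry the whole non-serious safety comparison.

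Several events in Table 1 are not specific to ultraviolet light: folliculitis, herpes simplex, bacterial infection and contact allergy can occur in either arm. A mild, short episode may be seen or mentioned at a session three times a week, yet be forgotten by an OTT patient whose week 4 and month 3 visits lie about two months apart. If such events are pooled with those elicited at visits, part of any excess under NB-UVB could reflect detection rather than harm, and the analysis could not tell the two apart unless the source is recorded. The same mechanism could make clinic treatment look less tolerable than home treatment if AEoSIs are ever tabulated by location.

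**Working it through.** The plan gives no figure to reproduce here. The check counts the opportunities for capture and then shows what unequal capture would do.

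**Inputs from the protocol article:** 3 sessions per week; course of 8 to 16 weeks, planned 12; follow-up visits at 4 weeks and 3, 6, 9 and 12 months; 134 evaluable patients per arm (Sample size). The share treated at home is not stated.

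**Sessions in clinic** = 3 × weeks:
- 8 weeks: 3 × 8 = 24
- 12 weeks (planned): 3 × 12 = 36
- 16 weeks: 3 × 16 = 48
- by week 13 (month 3): at most 3 × 13 = 39

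Adding the two common visits gives 24 + 2 = 26 to 39 + 2 = 41 contacts by week 13 for a clinic patient, against 2 scheduled follow-up visits for an OTT patient. The full 48 sessions run past month 3. For home treatment no nurse-run sessions are described, only remote monitoring.

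**Effect of unequal capture.** Let the true risk p be equal in both arms, and let d be the probability that an event is captured. Observed risk = p × d, so the false relative risk = d(NB-UVB) / d(OTT). The capture probabilities below are assumptions; the documents give none.

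| d(NB-UVB), all in clinic | d(OTT) | False relative risk |
|---|---|---|
| 0.9 | 0.8 | 1.125 |
| 0.9 | 0.7 | 1.29 |
| 0.9 | 0.5 | 1.80 |
| equal | equal | 1.00 |

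**Dilution by home treatment.** With home share h, and home patients captured like OTT patients, d(NB-UVB) = (1 − h) × 0.9 + h × 0.7:
- h = 0: 0.90 / 0.70 = 1.29
- h = 0.5: 0.80 / 0.70 = 1.14
- h = 1: 0.70 / 0.70 = 1.00

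**Chance of a false significant excess.** Take 0.9 against 0.7, all in clinic, 134 per arm, two-sided 5% test of two proportions:
- p = 10%: 9% vs 7%, difference 2 points, chance 8.7%
- p = 20%: 18% vs 14%, difference 4 points, chance 14.3%
- p = 30%: 27% vs 21%, difference 6 points, chance 20.8%

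With equal capture the chance in that direction would be 5% / 2 = 2.5%.

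**The case against.** The strongest reply is that the core method is the same in both arms. Patients are asked about AEoSIs at five common visits, and asking for start and stop dates is meant to recover events between visits. Every visit also includes a physical examination by the blinded assessor, although its purpose is disease severity. This stands. It means that a reader who infers from the AEoSI section alone that capture is only spontaneous or observed would be wrong. The two sections do not contradict each other either; the routes coexist. Common questioning equalises only the questioned part, however, and dates help only for events that the patient remembers.

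Other parts of the reply also stand:

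- The extra sessions apply to clinic treatment only. A reader might credit every NB-UVB patient with 24 to 48 staff contacts, but the NB-UVB section does not support that for home treatment.
- OTT patients have some contact beyond the two visits: nurse-led instruction, and extra visits at a switch or stop of therapy.
- Not every listed event is easily missed. Burning or pruritus needing management and eczema exacerbation are likely to surface at a visit, and striae, atrophy and pigment change may persist until one.
- Removing from the comparison whatever was first seen at a session could create the reverse bias. It would drop NB-UVB events that the patient would also have reported at a visit, while OTT keeps all of its own. The fix below is built to avoid this.

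Finally, form fields and safety tables belong largely to documents not shown. That is so, and the absence of a source field is not asserted here. The point rests on what the article itself fixes: all such events are analysed, whatever their source.

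**Conclusion.** The pooled between-arm comparison of mild shared AEoSIs is at risk of unequal ascertainment, most likely towards a higher NB-UVB rate. It is tempting to say that the safety comparison is biased. The documents do not support that: both arms are actively questioned on one schedule, and neither the capture probabilities nor the home share is given. The false relative risk could lie anywhere from 1.00 (no extra capture) to 1.29 under the 90% vs 70% assumption with all patients in clinic, and higher only if capture differed more.

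The direction rests on clinic sessions and tolerability monitoring bringing events to light that visit questioning would miss. The primary outcome and the sample size are untouched, and nothing in the article makes course length depend on a between-arm AEoSI comparison. The point is worth acting on because safety is a stated aim and, if source is not recorded, detection and harm may not be separable afterwards.

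**What to change.** 1. Record the source of each AEoSI report: scheduled visit, irradiation session, remote monitoring, or other spontaneous report. If the case report form already does this, only the tables below are needed.
2. Keep the table of all AEoSIs by arm as the main safety table. UV-specific events such as sunburn, and all SAEs, stay in it.
3. Beside it, give a between-arm comparison of events elicited with the same structured question and the same recall period at the five common visits. Count every event that the patient reports at a visit, including one already noted at a session.
4. Show events known only from sessions or remote monitoring separately within the NB-UVB arm, split by clinic and home.
5. State in the AEoSI section how the visit questioning and the open-ended capture fit together.

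The cost is one form field, one extra table and a sentence in the safety analysis. Recruitment began in February 2023, so events already on file would need their source filled in from the notes or classed as unknown. The visit-elicited comparison will hold fewer events and be less precise, which is why it stands beside the full table and does not replace it.

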##### Serious adverse events (SAEs)

A serious adverse event is defined as any untoward medical occurrence or effect that.Results in death;Is life-threatening (at the time of the event);Requires hospitalization or prolongation of existing inpatients’ hospitalization;Results in persistent or significant disability or incapacity; andAny other important medical event that did not result in any of the outcomes listed above due to medical or surgical intervention but could have been based upon appropriate judgment by the investigator.

An elective hospital admission will not be considered as an SAE.

The investigator will report all SAEs to the sponsor (Amsterdam University Medical Centers) without undue delay after obtaining knowledge of the events. The sponsor will report the SAEs through the web portal ToetsingOnline to the accredited MREC that approved the protocol, within 7 days of first knowledge for SAEs that result in death or are life-threatening followed by a period of a maximum of 8 days to complete the initial preliminary report. All other SAEs will be reported within a period of a maximum of 15 days after the sponsor has first knowledge of the SAEs.

##### Follow-up of AEoSIs and SAEs

All AEoSIs and SAEs will be followed until they have abated, or until a stable situation has been reached. Depending on the event, follow-up may require additional tests or medical procedures as indicated, and/or referral to the general physician or a medical specialist. SAEs will be reported according to GCP guidelines until the study ends for the patient (when all 6 visits are completed, when the patient discontinues prematurely, or when the study is prematurely terminated).

#### Amendments

Amendments are changes made to the study after a favorable opinion by the accredited MREC has been given. The MREC that gave a favorable opinion will be notified of all amendments. Should amendments to the study protocol occur, an update will be given to the clinical trial registry. Occasional deviations from the study protocol will be fully documented using a breach report form.

#### Dissemination plans

The investigators will adhere to the statement on publication policy made by the Central Committee on Research Involving Human Subjects (CCMO). The results of this trial will be published in peer-reviewed international medical scientific journals, preferably open access, regardless of the conclusions drawn about the investigational therapy. For knowledge sharing, (preliminary) findings will be presented at (inter)national research meetings and conferences. Participants will be informed of the results through a lay summary. This summary will additionally be disseminated to patients through the Dutch patient association VMCE.

## Discussion

The UPDATE trial aims to provide high-quality evidence of the effectiveness, cost-effectiveness, and safety of NB-UVB in the short- and long-term when utilized as a treatment option for patients with moderate-to-severe AE. It will contribute to current knowledge of NB-UVB as a phototherapy modality for AE [14], and will be helpful to determine whether NB-UVB has a place in the current treatment algorithm for AE [6].

Assessing NB-UVB in the setting of a randomized trial poses several challenges. During the drafting of the study design, these challenges have been carefully identified and addressed.

The first challenge in the design of this study concerned the choice of the appropriate control group. Eligible study participants are AE patients who require a next step in care. Use of a no treatment or placebo control group would mean denying the control patients further management of their moderate-to-severe AE, and, therefore was considered unethical. Additionally, such a design will inevitably lead to a large number of drop-outs in the control group. Since the topical treatment of the study population still leaves room for improvement, we deem OTT with clear but pragmatic and personalized instructions, an appropriate choice of control group. Therefore, we consider a pragmatic trial in which all participants are treated with OTT and that investigates the benefit of NB-UVB as an add-on to OTT, the most appropriate choice [43]. With this design in a closer to real-life setting that enables all patients to benefit from trial participation, we believe that the UPDATE trial will provide high-quality data that is easily applicable to clinical practice.

Another challenge concerns the study patients and physicians being aware of allocated treatment. Blinding is an important component to ensure valid trial results and minimal bias. However, blinding of NB-UVB treatment is deemed logistically infeasible, as this would require a placebo (such as a blue light panel) that is not readily available in an outpatient- or at-home setting. Taking patient safety and -ethics into account, the current study design is considered the best possible option. By introducing an independent outcome assessor who is blinded to treatment allocation, physician-reported outcomes are in theory protected from confirmation bias. Additionally, patients will be instructed to not disclose their allocated treatment to the blinded investigator. In the assessment of NB-UVB, however, it may be visible to some degree to blinded researchers if a subject is or was receiving phototherapy. As NB-UVB may cause redness and tanning of the skin, complete blinding of the outcome assessor will not be guaranteed. This may affect lighter skin types more than darker skin types, as redness and tanning may be more visible.

In addition to the study limitations, the issue of reimbursement of NB-UVB should be considered. In the Netherlands, the process of retracting reimbursement is already in effect, leading to the out-phasing of NB-UVB as a treatment modality in the AE algorithm. This single trial may not suffice to provide compelling evidence to reverse this trend, but will need to be consolidated through pooling with other studies in an updated systematic review and possible meta-analysis. We expect with our UPDATE trial to importantly contribute to this matter.

## Trial status

Date of start recruitment

February 22nd 2023.

Date of completed recruitment (approximate)

July 1st 2024.

